### Study setting and data collection

3.3.

Recruitment will begin after the start of the school year and the intervention will be carried out by the primary health care nurses throughout the school period (January/June 2022). Public or concerted (private schools which receive public funds or subsidies) schools in neighborhoods at risk of social exclusion from Terrassa, Manresa and Barcelona (Spain) will be invited to participate.

Before starting the intervention:

An interdisciplinary committee of nine experts reviewed the intervention program and protocol in order to validate the contents and to ensure the relevance and appropriateness of the activities included in the intervention. The committee includes two psychologists, one social worker, and six primary health care and school nurses. Additionally, two adolescents at risk were included in the committee to develop the intervention and ensure the engagement of participants.

These nurses will be trained during two training sessions about resilience and activities included in the intervention.

Researchers will contact the selected schools and will discuss the study with school directors and teachers, answering the questions and reviewing the consent forms. The representatives of the schools will sign the participation agreement.An online informative session for parents/carers will be held, where doubts will be solved.A letter with the informed consent and relevant information from the study will send to parents/carers by schools.Once the informed consent is returned from parents/carers, adolescents will receive a session with age-appropriate information about the study in their classroom conducted by their teachers and research team.Assent from the adolescents will be obtained.For adolescents who do not assent, each school will prepare another activity depending on each school. For example, readings sessions, time for studying or homework

Data collection will start in January 2022 and will finish in December 2022. Data will be collected at baseline, after 6 weeks of the intervention (Post-intervention I) and 24 weeks later (Post-intervention II; Figure 1). Data from participants will be obtained through self-reported questionnaires provided by researchers. Teachers at schools will assure the full completion of the questionnaires at the desired times (T1-T3). Data will be stored on a secure server during the study, following the Spanish regulations. Recruitment of participants will be reported according to CONSORT guidelines for clustered randomized trials (Ivers et al., 2011; Figure 2).

**Figure 1 fig1:**
[figure not shown]
Fostering resilience in adolescents at risk study: Template enrolment, intervention and assessments. Adopting from figure SPIRIT. W, week; CYRM-32, child youth resilience measure-32; BRCS, brief resilience scale; Item 1, “Are You Depressed or Sad?”

**Figure 2 fig2:**
[figure not shown]
Consolidated standards of reporting clinical trial (CONSORT) flow chart, explaining the study settings, and how and when data will be collected. *N*, number of schools that have been involved in the specified step. CYRM-32, child youth resilience measure-32; BRCS, brief resilience scale; Item 1, “Are You Depressed or Sad?”

### Intervention

3.4.

#### Intervention group

3.4.1.

The Fostering resilience in adolescent at risk (FRAK) intervention is a multicomponent intervention based on social and emotional learning, mindfulness and fostering protective factors. This intervention was developed according to the ecological framework, the empirical evidence and the contextual information. The contents, components, pedagogy, and technical elements of FRAK were established based on the IERM (Llistosella et al., 2022). Students will follow a training consisting of six 55-min sessions: (1) introducing resilience, (2) self-esteem, (3) emotional regulation strategies, (4) social skills, (5) problem-solving, (6) community resources, and social and peer support.

In order to decide which activities should be included in the final intervention we worked on three steps:

*First step*: The activities found in a previous systematic review were organized according to the protective factors with the greatest scientific evidence: resilience and coping; self-esteem; emotional regulation strategies, social skills, problem-solving, community resources, social and peer support, self-awareness, mindfulness, etc. (Llistosella et al., 2022).

*Second step*: A shared folder was created with all the material, to facilitate access to all members of the multidisciplinary expert committee. The mindfulness exercises were recorded on a podcast by a mindfulness expert and psychologist.

*Third step*: After two Delphi sessions, where the different activities were discussed and weighed, the intervention was designed.

The intervention group will receive six training sessions, each session will consist of 5 min of mindfulness, followed by 45 min of the corresponding activity and 5 min to explain the activity to do at home. All the activities included in the intervention will be dynamic and participatory; there will be no master classes. For this reason, the methodologies used will be real cases and role-playing. A complimentary reflective dossier was designed with individual activities to maintain the continuity of activities at home. More details about the sessions and their goals are presented in Table 1.

**Table 1 tab1:** Fostering resilience in adolescent at risk session’s outline.

Session goals	Activities
*Session 1:* **Introducing resilience and coping skills** Introduction to mindfulness. Introduction to conscious breathing Acquire mindfulness skills Learning the concept of resilience and coping	5-min Breathing space Describe the different protective factors according to the IREM model (individual and environmental factors). Recognize emotions through the body and strength resources. Put into perspective the impact of experiences of violence and discrimination during the course of their lives. The team resilience game: (1) participants from five groups; (2) Pick talent; (3) Write the talent on a name tag and put it on; (4) Each team one situation: Hurricane; Vandalism; Environment. How can your resilience team use their talents to cope with the situations? Reflexion and debriefing: What resilience skills are most useful in all situations? If you could add one resilience skill to your gear, what would it be and why? **Home practice:** Resilience Wheel: Identifying One’s Protective Factors
*Session 2:* **Self-esteem** Acquire mindfulness skills Increasing self-esteem and self-concept. Learning to value others positively and feel valued by them Expanding the repertoire of strategies to managestress Encouraging participants to bring strengths to the present to benefit their self-esteem and group integration.	5-min body scan, breathing space Development of the self-esteem definition and group reinforcement of self-esteem Express and recognize the qualities of peers: the peer in front will write a quality of the peer behind, then the one behind will communicate it and will write that of the next one and so on. Reflexion and debriefing: is there any model of family to develop good self-esteem? How many friends do I need to have good self-esteem?; What does school performance have to be like to have good self-esteem?; **Home practice:** Make an album with drawings, photos or any other resource with the themes: I live with…; What makes me feel better is…
*Session 3:* **Emotional strategies regulation** Acquire mindfulness skills Recognizing emotions in others and communicating one’s own emotions to others. Managing one’s own emotions and recognizing the emotion of anger and the resulting behavior	5-min body scan, breathing space Highway game and emotions: identify your unhelpful red thoughts (negative self-talk) and challenge them to come up with helpful green alternative thoughts (positive self-talk). Emotion check-in, psychoeducation about emotional regulation Reflexion and debriefing: what red useless thoughts make us feel sad, angry, and worried? what green thoughts make us feel happy, confident and brave? **Home practice:** Think of a situation that makes you very angry and try to capture it in an image
*Session 4:* **Social and communication skills** Acquire mindfulness skills Increasing knowledge of social skills. Learning the different styles of communication: aggressive, passive and assertive. Promoting assertive communication.	5-min body scan, breathing space A brief explanation of social skills and the three communication styles (passive, aggressive, assertive) Role-playing situations: “You meet a group of friends and there is a person you like a lot. He/she approaches you to talk and offers you a cigarette/alcohol, why he/she smokes or is consuming it. What would you do? Respond in an aggressive, passive, or assertive communication style. Reflexion and debriefing: how have you felt? how could we tell him to make him feel better? **Home practice:** Prepare your own “what would you do if…?.” To do this, prepare cards with situations to which it would be difficult for all of us to react (What would you do if… you have to do a job with someone you do not like?)
*Session 5:* **Solving problems, peers support and competence** Acquire mindfulness skills Promoting teamwork and personal competence. Increasing their ability to solve problems assertively and as a team. Learn to see the positive side of conflicts. Developing the capacity for reflection to solve conflicts. Promoting communication and dialog, to seek constructive solutions	5-min body scan, breathing space Life stories: different problematic situations identified by participants will be worked through the problem-solving technique (the participants work in teams to find solutions): (1) what is the problem? Define it, (2) brainstorm and list all possible solutions, (3) list what could happen for each solution, (4) select the best solution based on the consequences, (5) Make a plan for put the solution into practice and do it, (6) Evaluate the result in terms of strengths and weaknesses and, if it does not work, go back to step 2 and try again. Reflexion and debriefing: how have we resolved the conflict? **Home practice:** Resilience Wheel II: The purpose of the wheel is to identify one’s strengths and resources (Problems that I have solved, how I solve problems, that I can tell about myself…)
*Session 6:* **Community resources, social and peer support** Acquire mindfulness skills Learning about community resources Increasing community recourses	5-min body scan, breathing space Identify and learn the resources present in the community. Identify the possible barriers that can be found to access these resources and possible solutions to address them With the problems identified in session 5, the participants work in teams to find the different resources of the community to cope with these problems Closed activity: Make a mural on craft paper; large enough that all participants in 2–3 groups can contribute to the mural. They will be asked to represent on the mural what the group has meant to them, what they have learned, and their reflections. They will be provided with materials to make a group collage (draw, write) Guiding questions for the mural: how did you feel during these weeks? what do you feel you learned during the activities? what is the activity that you remember the most? what would you change or improve? what impacted you the most? what did they notice? **Home practice:** Resilience Wheel I: Identifying One’s Protective Factors

Eleven primary health care nurses will carry out the intervention. Ten of them are women with more than 10 years of professional experience with adolescents. The nurses will be trained by a resilience expert (principal researcher) during two formative sessions of one hour each, with the following content: (1) the concept of resilience and protective factors and (2) theoretical concepts and practical activities included in the intervention. In addition, the principal researcher will supervise the nurses, and meetings will be held weekly with the professionals during the intervention period. Nurses will carry out the intervention within their usual practice without receiving compensation or any other incentive to do it.

Students from four different schools will follow a 6-weeks training, consisting of weekly 55-min sessions.

To ensure adherence to the intervention of participants, primary health care nurses will carry out the six weekly sessions face-to-face during school hours with the teacher attending each of them. They will be done in groups of 25 to 30 students, depending on the school, but never more than 30 students, to facilitate the dynamics of the activities and participation.

#### Control group

3.4.2.

The control group will complete different activities depending on each school. As it has been stated: reading sessions, time for studying or homework, etc. They will fill in the same research questionnaires as the intervention group and during the same period (January to December 2022).

Schools in the control group will be all waitlisted to receive the intervention during the following academic year should if it proves to be effective.

#### Monitoring procedure and risk participants

3.4.3.

An independent monitoring committee will endorse the protocol and follow up on the process. This committee will meet regularly and evaluate the reports from researchers to assure and guarantee the rights and well-being of participants. The committee also will verify that the reported data are accurate and complete. The committee will be responsible for the overall supervision of the study. The following assessments will be conducted by the committee: (1) after the beginning of the study, (2) during the implementation of the intervention, (3) during follow-up, and (4) at the end of the study.

The research team agreed that in case of detecting a participant at clear risk (for example, depression), the nurses and the research team will inform the parents/carers. A list of public resources will be provided, and a visit will be suggested with the corresponding primary health pediatrician. The research team and nurses will follow up on the adolescent until the family contacts the referral pediatrician or during the study period. When necessary, the competent authorities in Social Services will be informed, to monitor the adolescent at risk. Confidentiality will be maintained to avoid the stigmatization of the participant.

### Outcomes measures

3.5.

#### Primary outcomes

3.5.1.

The level of resilience is the primary outcome, assessed using principally the Child youth resilience measure-32 (CYRM-32; Llistosella et al., 2019). Additionally, the Brief resilience scale (BRCS; Limonero et al., 2014) will be used.

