**Methods:**

The recruitment period started in January 2022. Schools will be randomly allocated to control and intervention groups by an external researcher using computer-generated random numbers. The minimum sample size was estimated to be 70 participants per group. Primary health care nurses will carry out the intervention during the school period (January to June 2022). Students will follow a specific training consisting of six 55-min sessions, for 6 weeks. Each session will consist of 5 min of mindfulness, followed by 45 min of the corresponding activity: introducing resilience, self-esteem, emotional regulation strategies, social skills, problem-solving, community resources, social and peer support, and 5 min to explain the activity to do at home. Data will be collected at baseline, 6 weeks, and 24 weeks after the intervention. The child youth resilience measure-32 (CYRM-32) scale will be used to assess the effectiveness of the intervention. This study received a grant in June 2021.

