##### Brief resilience scale

3.5.1.2.

The BRCS scale (Limonero et al., 2014; 4-items) is also a 5-point Likert scale to assess coping strategies to manage stress. Cronbach’s *α* for the scale was 0.7. Temporal stability at 6 weeks was measured by Pearson’s correlation, and its value was 0.69.

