### Sample size calculation

3.6.

Standard deviation (SD) of the primary outcome CYRM-32 scale was used to estimate the minimum sample required to detect a 10-point difference in the scale between the intervention and control groups.

Taking into account an SD of 20 of the CYRM-32 scale, accepting an alpha risk of 5%, power of 80% and a follow-up loss rate of 10%, it would be necessary a minimum of 70 students/group. GRANMO tool (Antaviana, 2011) was used to calculate the sample size.

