In the application of this intervention, we consider some limitations. On one hand, the effect of the intervention may be lost in the long term. However, a 24 weeks follow-up is proposed to assess the maintenance of the effect and see if it is necessary to include reinforcement or repeat the intervention after 1 or 2 years to maintain resilient results. On the other hand, there may be some disparities in the effectiveness of the intervention between schools due to the different teams involved. If this is the case, we will propose to improve the trainings so that the teams act as similarly as possible.

Once the intervention will be applied, we will be able to assess its effectiveness. We expect to increase resilience in adolescents at risk and prevent mental health problems through this school-based intervention. Once the effectiveness is demonstrated, nurses from different fields such as primary health care or mental health specialists will have access to the program to be implemented in schools or other sites that work with adolescents at risk. This intervention will give new tools to nursing professionals to increase resilience and coping skills for facing adverse situations during adolescence.

Currently, we have finished the recruiting period and the trial status is “active” at www.clinicaltrials.gov. At the end of the recruitment, we had a total sample of 674 participants from eight randomized schools. The intervention was carried out in 4 schools from January 2022 to spring 2022. We are analyzing the initial data from control and intervention groups at T1 (baseline) and T2.

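### CYRM-32 is ranked as the lead measure, but no primary time point is named, BRCS also stands under the primary heading, and T2 data are already being analysed

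*Protocol article*

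**What the plan says.** **Scales.** Section 3.5.1 has a plural heading and two subsections, one per scale. Its text ranks them: "The level of resilience is the primary outcome, assessed using principally the Child youth resilience measure-32", and then "Additionally, the Brief resilience scale (BRCS; Limonero et al., 2014) will be used". Section 3.5.1.2 says that BRCS "is also a 5-point Likert scale to assess coping strategies to manage stress". Secondary outcomes are listed separately in section 3.5.2, and BRCS is not among them. Two other places name CYRM-32 alone. The abstract says "The child youth resilience measure-32 (CYRM-32) scale will be used to assess the effectiveness of the intervention", and section 3.6 says "Standard deviation (SD) of the primary outcome CYRM-32 scale was used to estimate the minimum sample required to detect a 10-point difference".

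**Times.** Section 3.3 sets a baseline measurement and two follow-ups, Post-intervention I (T2) and Post-intervention II (T3). The abstract puts it as "Data will be collected at baseline, 6 weeks, and 24 weeks after the intervention". Neither follow-up is called primary anywhere, and the 10-point target in section 3.6 has no time point.

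**Analysis.** Section 3.9 compares the scores between groups with 95% intervals throughout and singles out no scale or time.

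**Status.** Section 3.8 says that participants and the research team are not blinded. The Discussion says: "We are analyzing the initial data from control and intervention groups at T1 (baseline) and T2".

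**The concern.** A primary endpoint consists of a measure and a time. The article comes close to fixing the measure and leaves the time open. With two follow-ups and a sample size built on one test, either follow-up could later be presented as the one the trial was designed for.

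Three features give this weight here:

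- T2 data from both arms are being analysed by an unblinded team, and the published text would not stop the time point being chosen in the light of those results.
- The Discussion itself foresees that an early effect may fade. No rule says whether a positive T2 with a null T3, or the reverse, counts as success.
- Decisions depend on the answer. Section 3.4.2 makes delivery to the waitlisted control schools conditional on effectiveness, and the Discussion plans wider access once effectiveness is shown. Neither ties effectiveness to a particular test.

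The choice of primary time belongs to the outcome definition in a protocol. It is not a detail usually left to an analysis plan.

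**Working it through.** **1. Reproduce the stated sample size.** Inputs from section 3.6: difference 10, SD 20, alpha 5%, power 80%, loss 10%.

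- n = 2 × (1.960 + 0.842)² × 20² / 10² = 2 × 7.85 × 4 = 62.8, so 63 evaluable per group.
- 63 / 0.90 = 70 per group, which matches the article.
- A one-sided test would give 50, then 56, which does not match.

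The plan is therefore sized for a single two-sided 5% comparison on CYRM-32.

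**2. Narrow reading: CYRM-32 at T2 or T3, each at two-sided 5%.**

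- Independent tests: 1 − 0.95² = 9.75%.
- Correlated tests: the T2–T3 correlation is not given. The two-month test–retest value of 0.695 for CYRM-32 (section 3.5.1.1) serves as a proxy. Simulating bivariate normal test statistics (2 million draws per setting) gives:

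| T2–T3 correlation | Chance of at least one false positive |
|---|---|
| 0.3 | 9.5% |
| 0.5 | 9.1% |
| 0.69 | 8.4% |
| 0.8 | 7.8% |

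The planned gap between T2 and T3 is 24 weeks, longer than the test–retest interval, so a correlation below 0.69 is plausible. Counting only false positives in favour of the intervention, the figure at 0.69 is about 4.2%, against a nominal 2.5%.

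**3. Upper reading: both scales at both times, four tests at 5%.**

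- Independent tests: 1 − 0.95⁴ = 18.5%.
- The correlation between CYRM-32 and BRCS is not in the document and is assumed to lie between 0.3 and 0.7. With a time correlation of 0.69, simulation gives 15.6% down to 13.7%. With time correlations of 0.5 to 0.8, the range is 16.9% to 12.8%.

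**4. What each remedy would need (same inputs).**

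| Primary comparisons | Two-sided alpha for each | Evaluable per group | Per group after 10% loss | Power with 63 evaluable |
|---|---|---|---|---|
| One, or a fixed sequence | 5% | 63 | 70 | 80.1% (first test) |
| CYRM-32 at both times, Bonferroni | 2.5% | 77 | 86 | 71.4% |
| Both scales at both times, Bonferroni | 1.25% | 90 | 100 | 62.1% |

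All figures ignore clustering, as section 3.6 does.

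**5. The time anchor.** The abstract can be read as placing T2 six weeks after the intervention ends. Section 3.3 places it after the six weeks of intervention. The two accounts of T3 can be read as agreeing, so the ambiguity concerns T2.

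**The case against.** The best defence is that the article does rank its measures. Section 3.5.1 puts CYRM-32 first and BRCS as an addition, and both the abstract and section 3.6 name CYRM-32 alone. That stands. A reader might infer from the plural heading that the trial has four equal chances of success at 5% each, but the text does not support this as the main reading. The follow-up times are also not under that heading; they come from section 3.3.

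The roles of the two times are partly described. The Discussion presents the 24-week measurement as a check on whether the effect lasts, which points to T2 as the main effect and T3 as its durability. This is a fair hint, but it designates neither as primary.

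A multiplicity rule may sit in an analysis plan that is not shown, and the article nowhere says that any one significant result means success. That also stands, so the absence of such a rule is not held against the article. The unnamed primary time is a different matter.

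A reader might also infer that T2 was compared between arms before T3 collection had finished. The Discussion does not report the status of T3, does not date its statement, and does not say that a between-arm test was completed. Finally, coping is part of the trial's own resilience model, so a coping scale alongside CYRM-32 is not an error in itself.

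**Conclusion.** The point holds in a limited form. CYRM-32 is the lead measure, but the time of the primary comparison is not fixed, and the place of BRCS under the primary heading is loose. Analysis of T2 data has begun in an unblinded trial, so the published text does not protect the choice of time.

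The firm ambiguity is CYRM-32 at T2 or T3. If either could be claimed as the primary result at 5%, the chance of a false positive is about 8% to 10% instead of 5%. The range of about 13% to 18.5% applies only if BRCS is treated as co-primary, and it rests partly on an assumed between-scale correlation. The 8.4% figure rests on a test–retest value standing in for the T2–T3 correlation. None of these figures allows for clustering.

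**What to change.** - Name the CYRM-32 total score at one stated time as the single primary endpoint, with weeks counted from one anchor used in both the abstract and section 3.3.
- Attach that time to the 10-point target in section 3.6.
- List BRCS under secondary outcomes.
- Test CYRM-32 at the other time only if the first test is significant, each at two-sided 5%. This fixed sequence keeps the overall error for the two tests at no more than 5%. The order T2 then T3 would fit the Discussion's account of the 24-week measurement.
- State openly that analysis of T2 data had begun when the choice was fixed, and whether results by arm had been seen. Disclosure does not restore full prespecification, but it lets readers judge the choice.

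The cost is wording. The minimum of 70 per group is unchanged, whereas splitting alpha would raise it to 86 or 100. The small downside is that a positive BRCS result, or one out of sequence, could no longer be called primary.
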